#### Enhanced usual care

Participants will receive EUC in both the intervention and control arms, as there is non-existent usual care for perinatal depression. The majority of cases of perinatal depression either remain unidentified or are classified as pregnancy blues in both settings. There is no provision of services for mothers with depression in the primary health-care system of Pakistan or in hospitals in Goa. EUC will comprise the following:Informing participants about their diagnosis of depression.Informing depressed participants about ways to seek appropriate health care (i.e. by going for assistance to their LHWs, to the primary health centre or to the tertiary health centre, which is the Institute of Psychiatry, Rawalpindi, Pakistan).In India, providing gynaecologists with the findings of the screening results for perinatal depression.Providing the primary health-care centres and the gynaecologists with the adapted WHO mhGAP treatment guidelines for perinatal depression [35].Providing an information sheet to all pregnant women about how and where to seek health care from including local Community Health Workers (CHWs), primary health facilities and tertiary care facilities, both during pregnancy and beyond.

### Outcome evaluation

The primary end point of the trial is 6 months postnatal; in addition, interim follow-up data will also be collected at 3 months postnatal. At each follow-up, consent will be reaffirmed by trained research assessment teams. The outcome assessment measures with the specific outcomes are given in Tables 1 and 2, and they are described briefly below.

#### Patient health questionnaire

PHQ-9 scores the nine DSM-IV symptom-based criteria for depression on a four-point Likert scale from not having the symptom at all, to having it nearly every day, over the last 2 weeks. The score for each item is summed to arrive at a total score. The cut-off point of 10 is selected as the most accurate value for the detection of depression [28] and has a high positive predictive value for the diagnosis of depressive disorder [29]. PHQ-9 has been translated into local languages and previously used in both Pakistan and India [30, 31].

#### WHO disability assessment schedule

The WHO disability assessment schedule (WHO-DAS) is a 12-item questionnaire for measuring functional impairment over the last 30 days. In addition, two items assess the number of days the person was unable to work in the past 30 days. It gives a total disability score, quality adjusted life years and number of days out of work. WHO-DAS has been validated for international use [36].

#### Client service receipt inventory

This questionnaire collects data on the utilisation and costs of health care and lost productivity (including that of caregivers). It will provide the costs of illness (both direct and indirect). It will be used at the 3- and 6-month follow-ups to cover costs of illness starting from antenatal to 6 months postnatal. Client service receipt inventory (CSRI) has been used in the study settings, and an adapted version will be used based on an international study on perinatal depression [37].

#### Multidimensional scale of perceived social support

The multidimensional scale of perceived social support is a 12-item questionnaire that measures the perceived social support of the mother. It has three domains of support: (1) significant other, (2) family and (3) friend. It is a based on a Likert scale and the higher the score, the more the perceived social support. It has been used in the study settings [22].

#### Exclusive breastfeeding

This will be based on 24-hour maternal recall using the WHO definition of exclusive breastfeeding. It has been used in the study settings [38, 39].

#### Infant anthropometry

Digital scales for weight and a tape measure for height (height mats) will be used. Z-scores for both weight for age and height for age will be calculated. This has been used extensively in the study settings [22, 40].

### Discontinuation criterion

Trial participants will be discontinued from the study if there is:Loss of baby or miscarriageDevelopment of a psychotic episodeDevelopment of a manic episode

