**Methods/Design:**

THPP is evaluated with two randomised controlled trials: a cluster trial in Rawalpindi, Pakistan, and an individually randomised trial in Goa, India. Trial participants are pregnant women who are registered with the lady health workers in the study area in Pakistan and pregnant women attending outpatient antenatal clinics in India. They will be screened using the patient health questionnaire-9 (PHQ-9) for depression symptoms and will be eligible if their PHQ-9 is equal to or greater than 10 (PHQ-9 ≥ 10). The sample size will be 560 and 280 women in Pakistan and India, respectively. Women in the intervention arm (THPP) will be offered ten individual and four group sessions (Pakistan) or 6–14 individual sessions (India) delivered by a peer (defined as a mother from the same community who is trained and supervised in delivering the intervention). Women in the control arm (enhanced usual care) will receive health care as usual, enhanced by providing the gynaecologist or primary-health facilities with adapted WHO mhGAP guidelines for depression treatment, and providing the woman with her diagnosis and information on how to seek help for herself. The primary outcomes are remission and severity of depression symptoms at the 6-month postnatal follow-up. Secondary outcomes include remission and severity of depression symptoms at the 3-month postnatal follow-up, functional disability, perceived social support, breastfeeding rates, infant height and weight, and costs of health care at the 3- and 6-month postnatal follow-ups. The primary analysis will be intention-to-treat.

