## Methods/design

### Trial settings

The trials will be conducted in rural and urban settings (the rural sub-district of Kallar Syedan, Rawalpindi, Pakistan, and peri-urban Goa, India, respectively). Table 3 provides information about the SHARE Pakistan and SHARE India study settings.

**Table 3 Tab3:** Study settings

Study settings	Pakistan	India
Study area	Kallar Syedan, one of the seven rural sub-districts of the district Rawalpindi	Three out of six sub-districts of North Goa district: Bardez, Bicholim and Tiswadi talukas.
Population	170,000	1,460,000
Average household size	6.2 members	4.2 members
Livelihood	Mainly subsistence farming, supported by serving in the armed forces or working as government employees and semi-skilled or unskilled labourers in the cities	Mainly tourism supported by mining and agriculture
Literacy rates	Males 80 %, females 50 %	Males 93 %, females 82 %
Infant mortality rates	84 per 1000 live births	9 per 1000 live births

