### Analysis

The quantitative analysis will be done using STATA (version 13) following CONSORT guidelines for individually randomised and cluster-randomised trials respectively. Flow charts will include the number of participants seen at each stage of the trial, including the number screened, eligible, randomised and analysed for the primary outcome. Initial analyses will compare baseline characteristics of enrolled participants by arm and follow-up status. The outcome measures will be summarised at baseline and the 3- and 6-month postnatal follow-ups by intervention arm, summarised by means (standard deviation), medians (interquartile range) or numbers and proportions as appropriate (and including age, gender and baseline outcome score). For continuous outcomes, histograms within each arm will be plotted to assess how closely the scales follow a normal distribution to determine how to describe the outcomes and how to do the inferential analysis properly.

The primary analyses will be ITT at the 6-month follow-up visit adjusted for the baseline measure of the outcome. In the Pakistan trial, mixed-effects logistic regression models will be used to analyse binary outcomes, adjusting for village clusters as random-effects variables and Union Councils as fixed effects. In the Indian trial, peers will be adjusted for as a random effect in the analysis. Analyses of continuous outcomes will use mixed-effects linear regression, additionally adjusting for the baseline value of the outcome. Adjustments will also be made for variables for which randomisation did not achieve a balance between the two arms at baseline.

Effect sizes will be reported as: (1) crude and adjusted relative risks estimated using the marginal standardisation technique with 95 % confidence intervals for the ratios estimated via the delta method [46] for binary outcomes, (2) and as mean differences and standardised mean differences, with 95 % confidence intervals for continuous outcomes. Missing data for the outcomes will be estimated using multiple imputation [47]. Secondary analyses will include repeated measures analyses of data collected at the 3- and 6-month postnatal follow-ups, which is efficient use of all available data.

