### Ethical considerations

The trial protocols have been granted ethical approval from the respective sites, the Institutional Review Board of Human Development Research Foundation (Pakistan), Institutional Review Board of Sangath (Goa, India), Indian Council of Medical Research, Observational/Interventions Research Ethics Committee of LSHTM, UK, and the Committee of Research Ethics at University of Liverpool, UK. Lastly, both trial protocols have ethical approval granted by the Global Mental Health DSMB of NIMH, USA.

Written (or witnessed or audio recorded, if the participant is illiterate) informed consent will be mandatory for enrolment. Separate consent will be taken for participation in the qualitative study. All participants will be able to access EUC, which represents a higher quality of care than what is currently available at both sites. We will protect the confidentiality of personal data principally through procedures to separate study data and participant-identifiable data. Quantitative data gathered in the tablets for each participant at baseline will retain personal identification items to minimise errors in transcribing identities, but these will be removed before transferring the data to STATA for analysis. We will monitor the occurrence of a number of specific SAEs, which include death of the participant due to any cause, suicide attempt, violence against the participant, stillbirth, miscarriage or loss of child, stigmatisation (due to the intervention), any violence towards others, in particular the participant’s children, hospital admission due to a psychiatric problem and hospital admission of the participant or infant due to a serious medical emergency. Their detection, appropriate response (involving an independent psychiatrist responding within 3 working days, if requiring immediate response) and reporting will be governed by the standard operating procedure approved by the DSMB, which sets out the a priori criteria for unblinding of adverse events (i.e. a statistically significant difference in prevalence between the two arms). SAEs will be compiled by the data manager and a blinded summary report shared with the principal investigators, local ethics committees and the DSMB.

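### Discontinuing women from the study after baby loss, psychosis or mania makes an obtainable primary outcome missing by design and undermines the intention-to-treat analysis

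*Protocol article*

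**What the plan says.** The section Discontinuation criterion states "Trial participants will be discontinued from the study if there is" one of three events: the woman loses the baby or miscarries, becomes psychotic, or becomes manic. It applies to all participants in both trials and does not separate stopping the intervention from stopping assessment.

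Other sections bear on this rule:

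- Outcome evaluation: "The primary end point of the trial is 6 months postnatal". The primary outcomes, remission and severity, are both maternal PHQ-9 measures.
- Analysis: "The primary analyses will be ITT at the 6-month follow-up visit adjusted for the baseline measure of the outcome", and "Missing data for the outcomes will be estimated using multiple imputation". The abstract also specifies intention-to-treat.
- Table 1 places the SAE form at the 3- and 6-month postnatal follow-ups.
- Ethical considerations lists "stillbirth, miscarriage or loss of child" among the monitored SAEs, and also psychiatric hospital admission. It leaves SAE detection, response and reporting to a standard operating procedure that the article does not reproduce.
- Table 3 gives infant mortality in the Pakistan area as "84 per 1000 live births", and 9 per 1000 in the India area.

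**The concern.** All three triggers occur after enrolment, and each is plausibly related to maternal depression. Scoring the PHQ-9 does not require a living infant. Following the rule therefore stops collection of a primary outcome that could often still be obtained. Reading it as a rule about treatment only fits poorly, because it also covers control women, who have no programme sessions to stop.

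Three things are at stake.

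- **Primary comparison.** Once these women are gone, no PHQ-9 is observed after such an event. Imputation must then rely on women who did not have one.
- **Balance between arms.** Removal could differ by arm. Peers, who work only with intervention women, are trained to detect and report SAEs (section Thinking Healthy Programme Peer-delivered), so a trigger may be noticed more readily in that arm. Infant loss itself could also differ.
- **Safety data.** On a literal reading, a discontinued woman does not attend the visits at which the SAE form is completed.

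**Working it through.** **1. The plan's own figures.** Table 4 gives power for 65 % vs 45 % remission, 38 % vs 22 % remission, and an effect size of 0.4. No alpha is stated, so I assume two-sided 0.05. Effective n per arm = n / [1 + (m − 1) × ICC].

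- Pakistan: n = 280 × 0.80 = 224 per arm and m = 14 × 0.80 = 11.2. Effective n is 224 / (1 + 10.2 × 0.07) = 130.7 for intervention and 224 / (1 + 10.2 × 0.05) = 148.3 for control. Using a t reference with 38 degrees of freedom, power is 91.6 / 81.8 / 90.1 %, against the stated 90 / 81 / 90 %.
- India: n = 140 × 0.85 = 119 per arm and m = 119 / 30. Effective n is 103.6 for intervention and 119 for control. Power is 85.4 / 74.4 / 84.5 %, against the stated 86 / 74 / 84 %.

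All six figures agree within 2 points. If discontinuation added 10 points to the planned loss (an assumption), power for 65 % vs 45 % by the normal approximation would fall from 92.2 to 90.1 % in Pakistan and from 85.4 to 81.1 % in India. Power is not the main issue.

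**2. How many women, Pakistan.** The only documented input is 84 per 1000, an area-wide figure. It is applied here as one live birth per woman.

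- Infant deaths in year 1: 560 × 0.084 = 47.
- Deaths before 6 months, assuming 75–100 % of these: 35–47.
- Miscarriage or stillbirth after enrolment, assumed at 2–5 %: 560 × 0.02 to 560 × 0.05 = 11–28.
- Total: 46–75 women, or 8–13 % of 560.

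The 20 % loss allowance is 0.20 × 560 = 112 women. The Power calculations section does not say whether it includes discontinuations.

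**3. How many women, India.** 280 × 0.009 = 2.5 infant deaths, about 1 %, plus miscarriage and stillbirth. No rate for psychosis or mania is given, so none is added in either country.

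**4. Effect on the between-arm difference.** Let retained women show 65 % vs 45 %, a difference of 20 points, and let a fraction q be discontinued in each arm.

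- If the discontinued women have the same 20-point effect, the difference in all randomised women is 20(1 − q) + 20q = 20, so there is no bias.
- If they have no effect, the difference is 20(1 − q), so the retained-women figure is too high by 20q. That is 20 × 0.08 = 1.6 to 20 × 0.13 = 2.6 points.
- If loss is unequal and no discontinued woman remits (an extreme case), 6 % intervention and 3 % control gives 0.65 × 0.94 − 0.45 × 0.97 = 61.10 − 43.65 = 17.45 points. With 3 % and 6 % it gives 63.05 − 42.30 = 20.75 points. The 20-point figure is then too high in the first case and too low in the second.

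**The case against.** The strongest reply is that nothing in the Analysis section removes discontinued women from the analysis set. The analysis is intention-to-treat with imputation, and the imputation model and its predictors properly belong in an analysis plan that is not shown. A reader might infer that the protocol breaks intention-to-treat or excludes these women, and the document does not support that. What remains is that no imputation model can supply PHQ-9 values after such events if the protocol stops collecting them.

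Other strong inferences also go too far:

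- *All three triggers are listed SAEs.* Only baby loss or miscarriage is. Psychosis and mania enter only through psychiatric admission.
- *Safety follow-up ends.* That is the literal effect of the rule combined with Table 1, but the unseen operating procedure may cover later events.
- *These are the highest-risk women.* This is plausible, but the document does not rank risk.
- *Measurements would be imputed for infants who died.* The article does not say whether such values count as missing.
- *Remission is biased by 2–3 points.* If discontinued women remitted at 20 % rather than 45 % (an assumption), the shift would be 0.08–0.13 × 25 = 2.0–3.3 points. That is a shift within one arm, not bias in the comparison.

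It is also fair to say that six months postnatal is not defined for a pregnancy without a live birth, and that an acutely unwell woman may be unable to be assessed or to re-affirm consent. These points limit what can be collected, but they do not justify a blanket end to follow-up.

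**Conclusion.** The point holds as a conflict between the discontinuation rule and the intention-to-treat analysis at 6 months. Followed literally, the rule makes the primary outcome missing by design for reasons plausibly related to it, and no other section repairs this.

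The likely size in Pakistan is 8–13 % of randomised women, resting on the area mortality figure and on assumed timing and pregnancy-loss rates. The resulting bias in the remission difference runs from none (equal effect) to about 1.6–2.6 points of overstatement (no effect), given equal discontinuation in both arms. With unequal discontinuation the direction is open. The problem is much smaller in India as far as infant deaths are concerned. It concerns the estimand, bias and safety data, and no stated sample size or power figure is wrong.

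**What to change.** Reconcile Discontinuation criterion, Analysis and Ethical considerations so that these events do not by themselves end outcome and SAE follow-up. Whether the intervention stops is a clinical matter on which this point takes no view. The text should state that:

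- unless the woman withdraws or cannot re-affirm consent, the PHQ-9, the other maternal measures and the SAE form are collected at the planned visits, timed from actual or expected delivery;
- she is analysed in the arm to which she or her cluster was randomised;
- infant outcomes are analysed among live infants and are not imputed after an infant death.

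The cost is sensitive visits to bereaved or unwell women, a visit-timing rule for pregnancies without a live birth, and an amendment agreed by the trial steering committee. Consent is already re-affirmed at each follow-up, so no new consent step is needed. The change cannot be made good afterwards, because measurements not taken at the visits cannot be recovered.

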### Minimisation of contamination

The risk and level of contamination will be monitored at the levels of the peers and participants. All peers will be instructed not to share any information about the study, and not to provide any support to other mothers in the community, other than the ones who are assigned to the peer for delivery of THPP. This procedure will be regularly reviewed at the peers’ monthly supervision meetings. For the Pakistan trial, the risk of contamination will be minimised by the cluster design. The intervention and control village clusters will be geographically separated and the chance of intervention cluster participants regularly meeting control cluster participants will be negligible. Apart from this, both trials also plan to carry out a social network analysis of participants at the 3- and 6-month postnatal follow-ups to capture if any sizeable contamination took place and to adjust accordingly in our final analysis, using a contamination-adjusted intention-to-treat (ITT) analysis. The extent of social networking will be assessed at the level of the participants so that statistical adjustments can be made through contamination-adjusted ITT analysis (complier average causal effect analysis) [41, 42].

### Masking

Due to the nature of the intervention, it is not possible to mask participants and peers to treatment allocation. However, outcome evaluation will be masked, as all outcome measures will be administered by trained research assessment teams (outcome assessors), who are non-residents of the study area, independent of the intervention and masked to treatment allocation of the participants. Furthermore, participants will be instructed not to disclose to the outcome assessors whether they are receiving the intervention or not. During all assessments, the primary outcome measure (PHQ-9) will always be completed first to minimise the risk of bias in the event of unmasking and, if it occurs, the point of unmasking will be recorded. Sensitivity analyses will be carried out to assess the effect of unmasking on the primary outcomes. The intervention and outcome assessment teams will not have any interactions during the trial since there will be separate locations and administrative management. The assessment teams will be told that they are evaluating two interventions and that there is genuine equipoise about which one is better.

### Fidelity of the intervention

Two types of indicator will be collated, in both trials, to evaluate the fidelity of the THPP intervention, namely, quantity and quality. Quantity indicators will include:Number and duration of sessions delivered; information will be collated from peer logbooks, which will record basic information about the session, such as date, time and duration of the sessionNumber of participants who complete the treatment and have a planned dischargeNumber of participants who are treatment failures or need referral to mental health specialist services for any other reason

#### SHARE Pakistan

In Pakistan, the quality of sessions delivered by peers will be assessed using a specifically designed competency checklist based on the six key areas of THPP and the ENACT scale (which is an 18-item assessment for common factors in psychological treatments), including task-sharing initiatives with non-specialists across cultural settings [43]. Peers’ level of competency will be assessed using this checklist, during trainings and monthly supervision meetings with role-playing and sessions conducted by peers in the field.

#### SHARE India

In India, the quality of sessions delivered by peers will be assessed using the therapy quality scale. This is an 18-item scale that consists of two separate subscales: treatment-specific skills, which are specific to an intervention (e.g., reviews previous session, assigns homework and involves family members), and treatment approach skills, which assess common counselling skills that the counsellor uses (e.g., using active listening, appropriate language and a collaborative approach). This scale is based on a 20-item therapy quality scale used to evaluate the delivery of a culturally adapted depression treatment (the Healthy Activity Programme) by lay health workers in primary health-care centres in Goa [44], which is known to have good psychometric properties [45]. For competency, the peers will be rated on their performance in standardised role-playing with specific checklists for each session.

All sessions will be audio recorded and 5 % of these will be purposively selected for transcription and rated for fidelity by psychological treatment experts. All peers and different sessions will be covered within the 5 %. This was not found to be acceptable to women in Pakistan during piloting of the intervention, therefore it was not proposed for the trial phase.

